The laboratory parameters that will be measured to assess efficacy and safety at each visit are shown in Table 1. The patients will receive face-to-face daily visit within the first week in research centers; thyroid pain, temperature, and adverse events (AE) will be assessed at each visit. Time periods required for the relief and complete resolution of thyroid pain will be recorded. Blood samples will be taken for the measurement of CRP and ESR in the first week. The patients will then receive telephone visits every 7–10 days. During each telephone visit, thyroid pain, temperature, and AEs will be investigated, medicine usage will be directed and recorded. If patients complain of pain in the tapering period, the tapering of the dosage will be delayed. In some cases with severe pain, the dosage will even increased; the dosage will then be tapered until the thyroid pain disappears. If PSL is tapered to a minimum dosage (i.e. 5 mg) for several days (3–7 days) with no thyroid pain, discontinuation of PSL will be considered and patients will receive a face-to-face visit. During the visit, physical examination (e.g. blood pressure and body weight) will be conducted and a blood sample will be taken for the measurement of thyroid function, liver function, kidney function, glucose level, CRP, and ESR. In addition, AEs will be collected. If SAT recurs after discontinuation of PSL, PSL will be administered again. During the treatment period, anti-ulcer drugs will be administered to some patients with a history of intestinal ulcer or who feel abdominal discomfort during treatment. A hepatologist will be consulted for possible antiviral therapy in patients with inactive hepatitis.

**Table 1 Tab1:** Study plan detailing the procedures

Study period	Screening	Intervention period				
**Visit number**	1	2	3*	4-x	x	x + n
Study interval	– 0–3 days	Randomization	1 week	Every 1 week	PSL discontinuation	Every 4 weeks
Visit window*			(±2 days)	(±2 days)	(±2 days)	(±7 days)
Telephone visit				√		
*Screening/Demography/Baseline*						
Written informed consent	√					
Inclusion / Exclusion criteria	√	√				
Demographics	√					
Physical examination, height, and weight	√					
Medical / Current conditions	√					
History of diabetes and complications	√					
*Intervention*						
Instruction of drugs		√	√	√	√	√
Thyroid pain (VAS)	√	√	√	√	√	
Thyroid tenderness	√	√	√	√	√	
Temperature monitor	√	√	√	√	√	
CRP and ESR	√		√		√	
Thyroid function	√				√	√

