### Outcomes

The primary endpoint is the time period (days) required for PSL treatment (including PSL treatment for recurrence).

Secondary outcomes include time periods (days) required for complete resolution of thyroid pain (defined as no thyroid pain and no tenderness), time periods required for the relief of thyroid pain (defined as at least 50% decline of VAS scores), percentage of relapse during treatment, and the total dosage of PSL. Safety outcomes include all the AEs, vital signs, and collection of clinical chemistry parameters.

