### Statistical methods

The primary and secondary outcomes will be analyzed based on the full analysis set. All outcomes will also be analyzed based on the per-protocol set. The security endpoint will be analyzed based on the safety analysis set. Supportive sensitivity analysis will be carried out based on the per-protocol set and safety analysis set, using the method of last observation carried forward. Descriptive analysis will be conducted for continuous variables such as time period required for PSL treatment, total dosage of PSL, body weight, blood glucose, blood lipids, and blood pressure. Indexes such as the percentage of relapse will be summarized using frequencies and percentages. The AEs and their incidence will be summarized. The mid-term analysis will be carried out at the end of the PSL treatment, before the follow-up study.

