### Sample size estimate

The present study is a non-inferiority trial. The primary endpoint is the time period (days) required for PSL treatment (including PSL treatment for recurrence). PASS 11.0 software (NCSS, LLC, Kaysville, UT, USA.) was used to estimate sample size.

According to the previous literature [17, 18], the mean time was around 36 days with a standard deviation of 12 days. With a one-sided alpha level of 0.05, group sample sizes of 38 and 38 will achieve the power of 81% to detect non-inferiority with the margin of 7 days and the standard deviation of 12 days. Considering a drop-out rate of 20%, a sample size of 90 patients with a 1:1 allocation rate (45 patients per group) was finally determined.

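### Glucose, blood pressure and weight have no scheduled reading between baseline and the 5 mg discontinuation visit, so they are poorly placed to show a 15 mg versus 30 mg difference; lipids are listed for analysis but not scheduled

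*Protocol article*

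**What the plan says.** **Outcomes and analysis.** Under Outcomes: "Safety outcomes include all the AEs, vital signs, and collection of clinical chemistry parameters". Statistical methods plans descriptive analysis of continuous variables, among them "body weight, blood glucose, blood lipids, and blood pressure". No test, hypothesis or power is attached to these four variables. The Background gives lower risk and greater safety of the 15 mg start as part of the trial's aim.

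**Baseline.** Table 1 ticks glucose and weight at screening. The Screening period section takes blood pressure after randomization as baseline. Its laboratory list does not mention lipids.

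**On the initial dose.** Patients attend daily in the first week for pain, temperature and adverse events. The only laboratory work named is this: "Blood samples will be taken for the measurement of CRP and ESR in the first week". Later contacts during treatment are by telephone.

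**At discontinuation.** The trigger is the same in both arms: "If PSL is tapered to a minimum dosage (i.e. 5 mg) for several days (3–7 days) with no thyroid pain". Stopping is then considered and the patient is seen in person. Blood pressure and weight are examined, and "a blood sample will be taken for the measurement of thyroid function, liver function, kidney function, glucose level, CRP, and ESR". Lipids are not in this list. The Treatment period section points to Table 1 for the laboratory parameters at each visit, and Table 1 has no lipid row.

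**The concern.** The trial contrasts two initial doses. For glucose, blood pressure and weight, the only scheduled post-baseline reading that the article names comes when both arms have tapered to the same dose. A short-lived rise during the initial phase could have faded by then. Unless someone measured it for another reason or it was reported as an adverse event, it would leave no trace. Similar values at discontinuation could then be read as evidence that the two starting doses have similar metabolic effects, when the reading was taken too late to tell.

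The lipid point is a plain inconsistency and needs no assumption about dose effects. One section promises a summary of a variable that no stated visit collects.

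**Working it through.** **1. The plan's own figure.** The article gives no figure for the metabolic variables. Its only calculation is for treatment duration (Sample size estimate): margin 7 days, SD 12 days, one-sided alpha 0.05, 38 per group, 81% power. Standard error = 12 × √(2/38) = 2.75 days; 7/2.75 − 1.645 = 0.90; power = Φ(0.90) = 81.5%, or 80.9% with the noncentral t. The figure reproduces. It is used below only for its group size.

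**2. Schedule by variable, from Table 1 and the text.**

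| Variable | Baseline | Week 1 | Telephone phase | Discontinuation |
|---|---|---|---|---|
| Glucose | Table 1 | not ticked | no | Table 1 and text |
| Blood pressure | text | not named | no | text |
| Weight | Table 1 | not named | no | text |
| Lipids | not listed | not listed | no | not listed |
| CRP, ESR | Table 1 and text | Table 1 and text | no | Table 1 and text |
| Adverse events | from randomization | yes | yes | yes |

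Table 1 has no blood-pressure row, and its weight row is ticked at screening only. For these two variables the table is therefore not exhaustive. For laboratory tests the text makes it the schedule.

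**3. Contrast in current dose.**
- Discontinuation: 5 − 5 = 0 mg/day.
- Week 1, at most: 30 − 15 = 15 mg/day. Visit 3 has a ±2-day window, and Study design lets group 2 taper by 5–10 mg after as few as 5 days. Some group 2 patients may thus be on 20–25 mg, a contrast of 5–10 mg/day. The range is 5 to 15 mg/day for patients on schedule.

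**4. Timing of the discontinuation visit.** This assumes no recurrence and no delayed taper. The shortest case has 3 days on 5 mg. The longest lets the 5 mg step run its full taper interval (14 days in group 1, 7 in group 2).
- Group 1: 14 + 7 + 3 = 24 days to 14 + 14 + 14 = 42 days, that is 10 to 28 days after the last 15 mg dose. If the 5 mg step is held to 7 days, the upper end is 35 days, 21 days after the last 15 mg dose.
- Group 2: 5 + 5 + 5 + 3 = 18 days (30, 20, 10, 5 mg) to 14 + 5 × 7 = 49 days (30 mg, then 25 down to 5 mg), that is 13 to 35 days after the last 30 mg dose.

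**5. Cumulative dose at that visit.**
- Group 1: 15×14 + 10×7 + 5×3 = 295 mg, to 15×14 + 10×14 + 5×14 = 420 mg.
- Group 2: 30×5 + 20×5 + 10×5 + 5×3 = 315 mg, to 30×14 + (25+20+15+10+5)×7 = 945 mg.

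The ranges overlap between 315 and 420 mg, but group 2 generally carries the larger exposure. The exposure contrast is therefore not zero.

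**6. What a faded effect would mean.** No metabolic SD or effect size is given, so this is illustrative only: standardized difference d, 38 per arm, two-sided 0.05, power = Φ(d/√(2/38) − 1.96). The d detectable with 80% power is (1.96 + 0.84) × √(2/38) = 0.64.

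| d | 0.8 | 0.5 | 0.25 | 0.1 |
|---|---|---|---|---|
| Power | 94% | 59% | 19% | 6% |

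An effect of 0.8 on the initial dose that had shrunk to 0.25 by discontinuation would usually be missed. How far it would shrink cannot be derived from the documents.

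**The case against.** The strongest reply is that an end-of-treatment reading is a defensible choice. The Background and Discussion hold that glucocorticoid risk depends on both dose and duration, and cumulative dose can differ widely at discontinuation. For weight, a late reading may even be the better one. This stands, and it limits the point to effects that track current dose.

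Three further replies also stand in part.
- Only descriptive summaries are planned, so no formal comparison is lost. A summary taken at an uninformative time can still mislead.
- A condensed article may leave visit-level vital signs to the full protocol, and Table 1 is visibly incomplete for them. The point is firmer for glucose than for blood pressure and weight.
- The Discussion concedes difficulty in comparing adverse effects. It attributes this to the short study period and does not mention the timing of measurements.

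A reader might go further and infer that the design cannot detect any metabolic difference, or that nothing is measured while the doses differ. The documents do not support either. The first needs a pure current-dose effect, which they do not assert. The second overlooks adverse events, temperature and CRP/ESR in week 1. Nor is this the trial's only safety information: hematology, liver function, creatinine and uric acid are also measured at discontinuation, and total prednisolone dose is a secondary outcome.

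**Conclusion.** The point holds in a limited form. Glucose has no scheduled value on the initial dose. Blood pressure and weight have none that the article names. At the one post-baseline visit where all three are named, the current-dose contrast is 0 mg/day, against 5 to 15 mg/day at an existing week-1 visit. The descriptive safety summaries are poorly placed to show an initial-dose effect on glucose or blood pressure, provided that the effect follows current dose. The size of the loss is unknown.

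On lipids, the supportable statement is that Statistical methods disagrees with the screening list, the discontinuation list and Table 1. It would be tempting to say that no patient will have a lipid value. The article leaves the clinical chemistry parameters unspecified under Outcomes, so that cannot be concluded.

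Neither point touches the primary endpoint. Both are worth correcting because the trial's stated aim includes greater safety and the correction is small.

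**What to change.** 1. In Table 1, add glucose to the week-1 blood draw already taken for CRP and ESR. Add blood pressure and weight at that face-to-face visit.
2. Give Table 1 a blood-pressure row, and tick blood pressure and weight at discontinuation, so that the table matches the text.
3. In Statistical methods, summarise by arm the week-1 change from baseline for these three variables alongside the discontinuation values. Keep it descriptive.
4. For lipids, either schedule them at the existing screening and discontinuation draws or delete them from the analysis list.

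The cost is one routine assay and one set of readings per patient, with no extra visit, plus the lipid assays if they are kept. According to Trial status, recruitment began in June 2019 and was expected to run to March 2021. Patients already past week 1 at the time of the amendment will lack the new values, so the week-1 summary should report how many patients contribute in each arm.

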### Outcomes

The primary endpoint is the time period (days) required for PSL treatment (including PSL treatment for recurrence).

Secondary outcomes include time periods (days) required for complete resolution of thyroid pain (defined as no thyroid pain and no tenderness), time periods required for the relief of thyroid pain (defined as at least 50% decline of VAS scores), percentage of relapse during treatment, and the total dosage of PSL. Safety outcomes include all the AEs, vital signs, and collection of clinical chemistry parameters.

### Statistical methods

The primary and secondary outcomes will be analyzed based on the full analysis set. All outcomes will also be analyzed based on the per-protocol set. The security endpoint will be analyzed based on the safety analysis set. Supportive sensitivity analysis will be carried out based on the per-protocol set and safety analysis set, using the method of last observation carried forward. Descriptive analysis will be conducted for continuous variables such as time period required for PSL treatment, total dosage of PSL, body weight, blood glucose, blood lipids, and blood pressure. Indexes such as the percentage of relapse will be summarized using frequencies and percentages. The AEs and their incidence will be summarized. The mid-term analysis will be carried out at the end of the PSL treatment, before the follow-up study.

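### The only named sensitivity analysis carries the last observation forward on a duration endpoint and leaves out the primary full analysis set, so it can mislead in either direction

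*Protocol article*

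**What the plan says.** The Outcomes section defines one elapsed time per patient: "The primary endpoint is the time period (days) required for PSL treatment (including PSL treatment for recurrence"). The secondary outcomes include two further times, to relief and to complete resolution of thyroid pain.

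The Statistical methods section sets the primary population: "The primary and secondary outcomes will be analyzed based on the full analysis set". It adds that all outcomes will also be analysed on the per-protocol set. It then describes a supportive sensitivity analysis "based on the per-protocol set and safety analysis set, using the method of last observation carried forward". That sentence does not name the full analysis set and does not say which outcomes it covers.

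The Sample size estimate section states "The present study is a non-inferiority trial" and plans for loss: "Considering a drop-out rate of 20" per cent, with 45 patients per group. The Treatment period section has a provision, for the low-dose arm only, under which termination is considered if pain persists at 2 weeks. A separate 3-day provision applies to both arms.

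**The concern.** LOCF needs a variable measured repeatedly on the same scale. Days on PSL is known only once treatment, including any re-treatment, has ended. What can be carried forward is the count of days at last contact, which is a lower bound on the true value. A patient lost on day 10 and still on drug would enter as a 10-day course, against a planning mean of about 36 days. An incomplete record becomes a very good result. The two pain times have the same difficulty, because a patient lost before the event has no event time to carry.

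The choice of sets adds to this. Incomplete durations matter most in the full analysis set, which carries the primary result, yet the analysis is attached to two other sets. A per-protocol set would commonly exclude most drop-outs, leaving LOCF little to act on there.

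At stake is whether the one named sensitivity analysis can tell a reader if the non-inferiority conclusion survives missing data.

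**Working it through.** **Inputs from the protocol article (Sample size estimate).** "With a one-sided alpha level of 0.05"; "group sample sizes of 38 and 38 will achieve the power of 81" per cent; "with the margin of 7 days and the standard deviation of 12 days"; mean about 36 days; 20% drop-out; 45 randomised per arm.

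**Step 1: reproduce the stated power.** Take the true difference as 0 (not stated, but it reproduces the figure). The standardised margin is 7 / (12 × √(2/38)) = 7 / 2.753 = 2.543. The normal approximation gives Φ(2.543 − 1.645) = Φ(0.898) = 81.5%. The noncentral t with 74 df gives 80.9%. The stated 81% is reproduced.

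**Step 2: what scoring at last contact does to the mean difference.** Let the standard arm have mean 36 and the low-dose arm 43, a true deficit equal to the margin. Let d be the drop-out fraction in an arm and c the mean score given to a drop-out. The arm mean becomes (1 − d) × true mean + d × c. Three assumed timings were used:

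- A, loss uniform over the patient's own course: c is half the true mean.
- B, loss at day 14: c is about 14.
- C, loss uniform over days 3–14: c is about 8.5.

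Examples:

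- 20%/20%, A: 0.9 × 43 − 0.9 × 36 = 38.7 − 32.4 = 6.3 days.
- 30%/10%, B: (0.7 × 43 + 0.3 × 14) − (0.9 × 36 + 0.1 × 14) = 34.3 − 33.8 = 0.5 days.
- 10%/30%, A: 0.95 × 43 − 0.85 × 36 = 40.85 − 30.6 = 10.25 days.

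**Step 3: simulation.** 45 per arm, normal durations with SD 12 floored at 5 days, drop-outs scored at last contact, 20,000 runs per scenario. Non-inferiority is declared when the one-sided 95% upper t limit for low minus standard is below 7 days. With complete durations, false non-inferiority at a true 7-day deficit is 5.0%, and power at no true difference is 86.8%.

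True deficit 7 days:

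| Drop-out low/standard | Mean estimated difference, days (A / B / C) | False non-inferiority (A / B / C) |
|---|---|---|
| 20% / 20% | 6.3 / 5.6 / 5.6 | 7.4% / 11.4% / 10.6% |
| 25% / 15% | 4.3 / 3.0 / 2.5 | 21.4% / 34.3% / 35.1% |
| 30% / 10% | 2.4 / 0.5 / −0.6 | 42.8% / 65.4% / 69.8% |
| 10% / 30% | 10.2 / 10.7 / 11.8 | 0.3% / 0.2% / 0.1% |

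No true difference:

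| Drop-out low/standard | Power (A / B / C) |
|---|---|
| 20% / 20% | 76.2% / 76.6% / 68.3% |
| 30% / 10% | 97.6% / 98.8% / 98.7% |
| 10% / 30% | 31.0% / 21.9% / 11.2% |

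In the equal drop-out case with no true difference, the loss of power comes from spread: the SD rises from 12 to about 14–15.

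The simulation applies LOCF to all 45 patients per arm. It therefore describes a set that keeps nearly everyone randomised. In a per-protocol set that excludes drop-outs, LOCF would change little.

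**The case against.** The strongest defence is that this is a supportive analysis. The primary decision rests on the full analysis set, with a per-protocol analysis beside it. That stands: a reader might take the 7–70% rates as the trial's type I error, and the article gives no ground for that.

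A reader might also infer that LOCF always favours non-inferiority. It does not. The direction depends on the true difference and on which arm loses more patients. Excess loss in the standard arm cuts the error below 1%, and equal loss with no true difference makes the claim harder to reach. Nor is every drop-out scored as an early finisher. Only those lost before their final PSL stop, or before re-treatment, are truncated, and a patient moved to the standard dose is not necessarily lost.

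It would also go too far to say that the full-set result is never checked. The per-protocol analysis offers some comparison, and the safety set may contain nearly the same patients. The article does not define how the safety set is grouped, so one cannot assert that it breaks the randomised comparison. Set definitions and the missing-data rule for the full set may be in an unseen analysis plan, and their absence is not the point here.

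Finally, the LOCF sentence names no outcome. It follows the safety-endpoint sentence and precedes a list that includes weight, glucose and blood pressure, where carrying a value forward is at least possible. Applying it to PSL days is the natural reading, but it is not stated. This narrows the criticism without removing it: the text does not exempt the duration outcomes, which include the primary endpoint.

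**Conclusion.** The point holds in a conditional form. The one sensitivity method that the article names does not suit PSL duration or the two pain times, because it understates the duration of anyone lost on treatment, and it is not attached to the primary analysis set. This is a poorly chosen stated method, not missing detail.

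At a true deficit equal to the 7-day margin, false non-inferiority in the supportive analysis is about 7–11% with the planned 20% loss in both arms, 21–35% at 25%/15%, 43–70% at 30%/10%, and below 1% at 10%/30%. With no true difference and equal loss, power falls from about 87% to 68–77%. The arm splits, the drop-out timing and the use of all 45 per arm are assumptions. The 2-week termination provision, which covers the low-dose arm only, makes excess low-dose loss plausible but does not establish it.

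An analysis whose error moves this far in either direction according to who is lost cannot show that the primary result is robust. It should be changed, but the flaw does not in itself invalidate the primary analysis.

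**What to change.** - Remove LOCF for PSL duration, time to relief and time to resolution. If it is kept for any safety measurement, say which.
- Run the sensitivity analysis on the full analysis set by randomised group, treating a patient lost on PSL as having at least the observed days. Use multiple imputation of the remaining duration, bounded below by those days, with a penalty or tipping point for low-dose drop-outs.
- A censored analysis of PSL days may be added if its assumption of non-informative loss is stated. A patient lost while still in pain and on drug would violate that assumption, so it should not stand alone.
- Treat time to relief and time to resolution as censored at last contact.
- Do not use the safety set for efficacy.

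The cost is a change of wording, a little programming, and possibly a wider interval in the sensitivity analysis. No additional patients or visits are needed.

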24 h I-131 uptake or thyroid scintigraphy	√					
Hematology panel	√				√	
Liver function	√				√	
Creatinine, uric acid	√				√	
Glucose	√				√	
AEs		√	√	√	√	√

*AE* adverse event, *CRP* C-reactive protein, *ESR* erythrocyte sedimentation rate, *VAS* visual analog scale

*The patients will receive face-to-face daily visit within the first week in research centers; thyroid pain, temperature, and AEs will be assessed at each visit

About 50% of patients have an initial thyrotoxic phase due to unregulated release of performed thyroid hormones from damaged thyroid follicular cells [3]. The thyrotoxic phase usually lasts 3–6 weeks, ending when the thyroid stores of preformed hormones are depleted. About 30% of patients subsequently enter a hypothyroid phase that can last up to 6 months. In the present study, anti-thyroid drugs will have no role and beta-blockers will be used as needed to control thyrotoxic symptoms. Levothyroxine will be employed when patients have a TSH level above 10 mIU/L or symptoms during the hypothyroid stage. In addition, although viral infection is regarded as the possible cause of SAT, antiviral medications will not be suggested in the study.

After the discontinuation of PSL, patients will be invited to participate in the following observational study in which a 3-month face-to-face visit will be planed. The details of the follow-up study will be described elsewhere.

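### The primary endpoint counts PSL days for recurrence, but no common period after discontinuation is fixed in which recurrence counts, so those days may be captured incompletely or over unequal periods

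*Protocol article*

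**What the plan says.** Outcomes defines the endpoint thus: "The primary endpoint is the time period (days) required for PSL treatment (including PSL treatment for recurrence"). The Abstract and Sample size estimate repeat it. Treatment period makes clear that recurrence after stopping is included in trial treatment: "If SAT recurs after discontinuation of PSL, PSL will be administered again".

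Three other statements bear on whether those days are seen.

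- **Analysis time.** Statistical methods dates one analysis: "The mid-term analysis will be carried out at the end of the PSL treatment, before the follow-up study".
- **Status of follow-up.** Treatment period says: "After the discontinuation of PSL, patients will be invited to participate in the following observational study in which a 3-month face-to-face visit will be planed". It adds: "The details of the follow-up study will be described elsewhere".
- **Visit schedule.** Table 1 has an x + n column, every 4 weeks, placed under the intervention period. Drug instruction, thyroid function and adverse events are ticked there. The row "Thyroid pain (VAS") is ticked up to PSL discontinuation and blank at x + n, as are tenderness, temperature, and CRP and ESR.

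The related secondary outcome is "percentage of relapse during treatment", without saying whether relapse after stopping belongs to it.

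**The concern.** A total of treatment days that includes re-treatment has no defined end unless the plan says for how long after stopping a restart still counts. Here the endpoint looks past discontinuation, the dated analysis stops at it, and the period in between is assigned both to a separate invited study (text) and to the trial's own schedule (Table 1).

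The trial is open-label and tests a lower initial dose for non-inferiority. If recurrence after stopping is more frequent on the lower dose, uncounted days shrink that arm's excess and make non-inferiority easier to declare. The Discussion also uses a non-inferior duration to infer fewer adverse effects, so an undercount would weaken that inference too. If post-discontinuation data come only from patients who accept an invitation, the full endpoint would be known in a selected subset of the randomised patients.

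**Working it through.** **1. The plan's own figure.** Inputs from Sample size estimate: margin 7 days, SD 12 days, one-sided alpha 0.05, 38 per group, stated power 81%. A true difference of 0 is assumed.

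- Standard error = 12 × √(2/38) = 2.753 days.
- 7 / 2.753 = 2.543. Normal approximation: Φ(2.543 − 1.645) = 81.5%. Noncentral t with 74 df: 80.9%.

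The 81% reproduces. The concern is not with this figure, but the same set-up serves to size the problem.

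**2. The sections side by side.**

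| Question | Where | Answer |
|---|---|---|
| Do recurrence days count? | Outcomes | Yes |
| Is PSL restarted after stopping? | Treatment period | Yes, no time limit |
| How long after stopping does a restart count? | Nowhere in the article | Not fixed |
| When is the dated analysis? | Statistical methods | End of PSL, before follow-up |
| Who is followed after stopping? | Treatment period text | Those who accept an invitation; a 3-month visit |
| Who is followed after stopping? | Table 1 | Every 4 weeks, within the intervention period |
| Is recurrence assessed then? | Table 1, x + n | Pain, tenderness, CRP, ESR blank; drug instruction and adverse events ticked |

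**3. Possible size.** The article gives neither a recurrence rate nor a re-treatment length, so both are assumed: a between-arm difference in post-discontinuation recurrence (low-dose minus standard) of 0 to 20 percentage points, and re-treatment of 14 to 36 days. The upper length borrows the 36-day planning mean for the whole endpoint. If none of these days were seen:

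hidden shift = difference in recurrence × re-treatment days

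| Difference | 14 days | 28 days | 36 days |
|---|---|---|---|
| 0 points | 0 | 0 | 0 |
| 5 points | 0.7 | 1.4 | 1.8 |
| 10 points | 1.4 | 2.8 | 3.6 |
| 15 points | 2.1 | 4.2 | 5.4 |
| 20 points | 2.8 | 5.6 | 7.2 |

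At 10 points the shift is 1.4/7 = 20%, 2.8/7 = 40% or 3.6/7 = 51% of the margin.

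**4. Effect on the test.** Suppose the true difference in the full endpoint is exactly 7 days, so a correct test declares non-inferiority 5% of the time. With a hidden shift s the observed difference averages 7 − s, and the noncentrality is s / 2.753 (38 per group, SD kept at 12, noncentral t, 74 df).

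| Hidden shift (days) | Noncentrality | Chance of declaring non-inferiority |
|---|---|---|
| 0 | 0 | 5% |
| 1.4 | 0.509 | 12.7% |
| 2.8 | 1.017 | 26.2% |
| 3.6 | 1.308 | 36.3% |
| 7.2 | 2.615 | 82.8% |

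These are upper values for each scenario, because they assume that every recurrence day goes unrecorded.

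**The case against.** The strongest reply is that the endpoint is days on PSL, not a pain score. A restart is trial treatment, and Table 1 schedules drug instruction and adverse events every 4 weeks after discontinuation, so renewed PSL could be recorded without a VAS score. This stands: a reader might infer that recurrence days will be missed, and the article does not show that. It shows only that their capture is not secured for all patients.

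The dated analysis is called mid-term and is not said to be the final or only primary analysis. End of PSL treatment could also be read to include re-treatment, since the endpoint does. Data management withholds data from doctors and statisticians until patient evaluations are complete. So a reader might infer that the primary result will be fixed before recurrences can happen, and this too is unsupported. Recruitment runs from June 2019 to March 2021 and the planning mean is 36 days, so if the analysis waits for the last patient, most patients would be well past discontinuation. That reading, however, gives early recruits many months of observation and the last ones almost none, which is the unequal-period problem.

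Two further inferences go too far. The first is that the bias must favour non-inferiority: the arms also differ in taper, and the article gives no recurrence rates from which to fix the direction. The second is that the primary comparison will be tested twice at one-sided 0.05: no between-arm test is stated for the mid-term analysis, and testing rules may sit in an analysis plan not shown.

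Finally, follow-up details are deferred elsewhere and an article condenses. What it does state about endpoint, schedule, analysis time and follow-up nevertheless does not fit together, and the extent of the primary endpoint belongs to this trial, not to the follow-up study.

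**Conclusion.** The point holds in a limited form. The primary endpoint reaches past discontinuation with no common window, and the passages on re-treatment, follow-up, Table 1 and analysis time need to be reconciled. As written, recurrence days may be captured incompletely or over unequal periods.

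The size cannot be derived from the article. Over the assumed ranges the hidden shift runs from 0 to 7.2 days against a 7-day margin. Only the extreme corner, a 20-point difference with a full 36-day second course and no capture at all, exceeds the margin. The more moderate 10-point case already multiplies the 5% error rate about 2.5 to 7 times (12.7/5 to 36.3/5). The bias is towards non-inferiority only if the low-dose arm recurs more after stopping.

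This should be fixed; confidence is moderate, because a later analysis and recording of renewed PSL at x + n are both compatible with the text.

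**What to change.** Reconcile Treatment period, Table 1, Outcomes and Statistical methods as follows.

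1. Set one fixed recurrence window after first PSL discontinuation for every randomised patient, within the main trial. The 3 months already planned for the observational study is one candidate.
2. At the x + n visits, record PSL use and recurrence (pain and tenderness) alongside the items already ticked.
3. Run the primary non-inferiority test once, after the last patient completes the window. Keep any end-of-PSL look descriptive, with no between-arm test of the primary endpoint.
4. State whether the relapse outcome covers the same window.

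The cost is a protocol amendment, a few case report form fields, follow-up contact with all patients and not only those who accept an invitation, and a primary readout about 3 months later. The article reports recruitment as ongoing; post-discontinuation data not collected at the time are hard to recover reliably, so the change is best made early.
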